**FIGURE 2 nop21414-fig-0002:**
[figure not shown]
Diagram of the study

#### Data analysis

3.8.9

After checking the normal distribution of data by the Kolmogorov–Smirnov test, the data will be statistically analysed in SPSS.

The participants' demographics and clinical information will be described by frequency distribution and percentage for qualitative data and mean and standard deviation for qualitative data.

The groups' pre‐ and post‐intervention mean scores of SOC and FOC will be compared by the independent sample *t* test and ANCOVA, respectively. In addition, analysis of variance with repeated measures based on the Greenhouse–Geisser test will be employed to compare the pre‐ and post‐intervention mean scores of SOC and FOC in each of the two groups.

The two groups will also be compared before and after the intervention using a chi‐square test to select the delivery method.

It is noteworthy that nonparametric tests will be used if the data are not normally distributed. The significance level in all tests will be 0.05. If there is missing data, the missing data will be handled using statistical methods.

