#### Quantitative study

3.4.3

Is training intervention effective in reducing FOC among Iranian nulliparous women?Is the training intervention effective in increasing the choice of vaginal delivery among nulliparous women?Is the training intervention effective in increasing the SOC mean score among nulliparous women?

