#### Study design, participants and setting

3.8.1

In this educational trail RCT, the statistical population consists of all nulliparous women visiting comprehensive health service centres of Bostanabad.

The inclusion criteria are being nulliparous, being at gestational age 6 to 12 weeks (The first trimester of pregnancy is selected to better manage the FOC from the beginning of pregnancy and follow‐up to maintain the intervention for 6 months during pregnancy), being 18–35 years old, having a high school diploma or higher educational degree, no history of depression or long‐term medical illness in the past, singleton pregnancy, ultrasound confirmation of foetal health, no history of miscarriage or stillbirth, no contraindications for vaginal delivery during the study until the end of pregnancy, not being graduated in midwifery or relevant majors and willingness to participate in the study. The exclusion criteria are also emergencies requiring preterm delivery, indications for caesarean section, a history of caesarean section, a history of infertility, irregular attendance in training sessions, refusal to complete the questionnaire and no access to the participant for any unpredictable reason.

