#### Intervention

3.8.4

Based on successful evidence in this area (Bonmatí‐Tomas et al., 2019; Heggdal, 2015; Heggdal & Lovaas, 2018; Odajima et al., 2017; Tan et al., 2014, 2016), the training intervention will be performed in four sessions of at least 30 min by using appropriate audio‐visual training methods and tools to investigate each of the common factors of FOC obtained from the qualitative and review phases of this study. It is noteworthy that there would be changes in the number and duration of sessions based on the content obtained from the first and second phases of the study. Training sessions will be held in person probably in four groups of six and two groups of seven. However, the size of the groups may be determined depending on the conditions of the study group, the location of sessions and the number of samples selected from each centre. If the COVID‐19 pandemic reaches a stable state, the training sessions will be held under appropriate physical distancing and health protocols.

For the ease of group management and convenience of participants, training sessions will be held once a week for each group in the relevant, comprehensive health centre. After obtaining written consent from the participants to participate in the study, they will complete the questionnaires in the pre‐test phase. The person who will lead the sessions is a Ph.D. student in health education and health promotion.

Training sessions are taking place based on the priority of the educational domain (cognitive, emotional and behavioural). The first training sessions are based on the cognitive domain includes increasing comprehensibility and identifying GRASs, the next session based on the emotional domain includes increasing meaningfulness, and the last session based on the behavioural domain includes increasing manageability, respectively.

Since the qualitative phase of the study is conducted with a directed content analysis approach, the codes obtained from this phase are categorized as themes based on the components of ST. If these codes are common with the factors of the review phase of the study, the training content will be designed for this theme.

For other codes that are not included in these components of ST and form a new theme, if they are common with the factors obtained from the review phase of the study, the training content will be designed for the new theme.

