#### Data collection

3.8.5

The measurement tools of this study are a demographics questionnaire, the Wijma Delivery Expectancy/Experience Questionnaire (W‐DEQ), Antonovsky's sense of coherence scale (SOC), and a choice of delivery method checklist. All these tools will be completed by participants themselves (self‐reporting). It is noteworthy that there would be changes in the measurement tools depending on the component obtained from the first and second phases of the study.

The W‐DEQ was developed by the Sweden Klaas Wijma in 1998 (Wijma, Wijma, & Zar, 1998). The W‐DEQ is a short, practical and common tool for evaluating FOC (Badaoui et al., 2019). This tool consists of 33 items that are scored based on a 6‐point Likert scale (from 0: very much to 5: not at all). The total score on this scale ranges between 0 and 165, and higher scores indicate higher levels of FOC. As the cut‐off point of this scale is 85, scores over 85, under 38, between 38 and 65 and between 66 and 84 represent clinical fear, mild fear, moderate fear and severe fear, respectively.

The 13‐item Antonovsky's sense of coherence scale (SOC‐13) measures comprehensibility (5 items), manageability (4 items) and meaningfulness (4 items) (Antonovsky, 1993). The items are scored based on a 7‐point Likert scale and the total score on this scale ranges between 13 and 91. A score within the ranges 13–60, 61–75 and 76–91 indicates low, moderate and high levels of SOC, respectively (Voogand et al., 2020).

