#### Outcome variables

3.8.7

Reduced FOC and the selection of vaginal delivery are the primary outcomes and SOC is considered the secondary outcome of the training intervention in this study.

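### The post-intervention comparison of delivery choice, a primary outcome, ignores the pre-test choice already collected; the test is valid, but it can lose precision and leaves chance baseline imbalance uncorrected

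*Protocol article*

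**What the plan says.** All references are to the protocol article.

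- **Question (3.4.3):** whether the training is "effective in increasing the choice of vaginal delivery among nulliparous women".
- **Status (3.8.7):** "Reduced FOC and the selection of vaginal delivery are the primary outcomes"; sense of coherence is secondary.
- **Eligibility (3.8.1):** "The inclusion criteria are being nulliparous, being at gestational age 6 to 12 weeks", followed by further criteria. None concerns the delivery method the woman currently prefers.
- **Randomisation (3.8.3):** blocks of 4 and 6, with no stratification by preferred method stated.
- **Measurement (3.8.5, 3.8.4):** the tools include "a choice of delivery method checklist". After consent, "they will complete the questionnaires in the" pre-test phase. Since 3.8.9 compares the arms on choice before training, pre-test choice is collected.
- **Analysis (3.8.9):** for delivery choice, "The two groups will also be compared before and after the intervention using a" chi-square test. No covariate or stratum is named. For fear of childbirth and sense of coherence, the pre-test means get a t test and the post-test means ANCOVA. The covariate is not named, but the baseline score is the natural reading.
- **Time points (3.3, 3.8.4):** choice during pregnancy and the delivery method reported after childbirth are separate items.

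**The concern.** A woman's choice at 6 to 12 weeks may well predict her later choice. If it does, leaving it out of the later comparison has two effects. Variation that could have been explained stays in the error term, so power is lower than it need be. Also, if one arm happens to start with more women choosing vaginal delivery, part of that gap reappears in the post-intervention difference, with nothing in the analysis to remove it. The separate pre-intervention chi-square does not help: it tests whether the arms differ at baseline but does not correct the later comparison.

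The two primary outcomes are also handled differently. Fear of childbirth appears to be analysed with its baseline, while delivery choice is not. The sample size was set on a subscale of sense of coherence, so delivery choice has no planned power in reserve.

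**Working it through.** **Inputs from the article.** 38 per group, two-sided 5% level, 80% power, 20% attrition; means 23 and 20 with SDs 4.8 and 3.7 (3.8.8).

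**The plan's own figure.** (1.96 + 0.84)² × (4.8² + 3.7²) / (23 − 20)² = 32.03 per group; 32.03 × 1.2 = 38.4, so the stated 38 is reproduced. It rests on the meaningfulness subscale. With 20% lost, 38 × 0.8 = 30.4, so about 30 per arm are analysed.

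**Assumptions.** The article gives no rate of choosing vaginal delivery at entry and no persistence rate. I take 50% at entry; the 50.77% national caesarean rate in the Introduction is context only. Let r be the share of initial vaginal choosers who keep that choice and c the share of the others who move to it.

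**1. How often the arms differ at entry.** The SD of the baseline difference is √(2 × 0.5 × 0.5 / n), which is 11.5 points at n = 38 and 12.9 points at n = 30. Exact binomial probabilities:

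| Gap | 38 per arm | 30 per arm |
|---|---|---|
| At least 10 points | 42% | 52% |
| At least 15 points | 21% | 25% |

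**2. How much of a gap carries over.** With no training effect, the expected post-intervention difference is the baseline gap × (r − c). For a 10-point gap:

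- r = 90%, c = 10%: 10 × 0.80 = 8 points
- r = 85%, c = 20%: 10 × 0.65 = 6.5 points
- r = 75%, c = 25%: 10 × 0.50 = 5 points
- r = 65%, c = 35%: 10 × 0.30 = 3 points

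**3. Error rates with no true effect (simulation).** Over all randomisations the chi-square rejects in about 5% of trials, as it should. Among trials with a baseline gap of at least 10 points in either direction, it rejects in about 9% (8.5 to 11.5% across the strong-persistence scenarios) and a Mantel-Haenszel test stratified by pre-test choice in about 5%. At 75%/25% persistence and 30 per arm, the chi-square figure is about 7%.

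**4. Power at 38 per arm (simulation, 50% at entry).** The overall difference is 0.5 × the difference in switching, since retention is equal in both arms.

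| Kept in both arms | Switch, control v training | Overall difference | Chi-square | Stratified |
|---|---|---|---|---|
| 85% | 20% v 60% | 20 points | 44% | 53% |
| 90% | 15% v 50% | 17.5 points | 34% | 49% |
| 75% | 25% v 65% | 20 points | about 43% | 3–4 points more |
| 65% | 35% v 75% | 20 points | 43% | 43% |

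At 30 per arm, the first row becomes about 35% against 44%. I re-ran these scenarios and the exact probabilities, and they agree to within about one point.

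**The case against.** Three stronger readings are tempting, and the article supports none of them.

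**That two separate tests cannot answer a question about an increase.** The arms are randomised, so the post-intervention difference in proportions is an unbiased estimate of the training effect, and chance imbalance is already allowed for in the nominal 5%. The planned test does answer the question. The 9% figure is conditional on having drawn an imbalanced trial.

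**That women who already choose vaginal delivery cannot be moved and only dilute the effect.** They enter in the first trimester, and the article says fear peaks in the third. Training could keep some from drifting to caesarean. If it raised retention from 85% to 95%, with switching still 20% v 60%, the chi-square's power at 38 per arm would rise from about 44% to 64%. These women can carry signal.

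**That eligibility should have been restricted by current choice.** The programme is aimed at nulliparous women generally, so enrolling them all is a legitimate target population. Adjusting for pre-test choice would not change that population either.

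It is also fair to say that the power gain rests on persistence, which the article does not give and which may be weaker for the delivery method reported after childbirth than for choice during pregnancy. The contrast with ANCOVA depends on reading the unnamed covariate as baseline.

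What stands is narrower: a baseline value already collected for a primary outcome is left out of a stated analysis, and using it would cost no power to speak of in any scenario examined. Because 3.8.9 names the test, this concerns a stated choice and is not a detail left to an unseen analysis plan.

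**Conclusion.** The concern holds as a point about efficiency and about the estimate in the realised trial. It is not a finding of bias or of an invalid test. If half the women choose vaginal delivery at entry, a baseline gap of at least 10 points is close to an even chance (42% at 38 per arm, 52% at 30), and the planned comparison would pass on part of it uncorrected. The conditional rejection rate of about 9% against about 5% assumes strong persistence. The power gain at 38 per arm runs from about 10 to 15 points when 85–90% keep their early choice, through 3 to 4 points at 75%, to none at 65%. Both the entry rate and the persistence are assumptions, so the gain should be quoted as this range and not as a single figure.

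**What to change.** In 3.8.9:

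- Compare post-intervention choice between arms with adjustment for the woman's own pre-test choice, by a Mantel-Haenszel test stratified by it or by logistic regression on arm and pre-test choice. Do the same, separately, for the delivery method reported after childbirth.
- Report an adjusted risk difference.
- Show pre-test choice by arm descriptively in place of the pre-intervention chi-square.
- Report switching among women not choosing vaginal delivery at pre-test as descriptive only. At 50% this is about 0.5 × 38 = 19 women per arm, or 0.5 × 30 = 15 after attrition.

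Eligibility stays as it is. The cost is a few sentences of analysis wording. The checklist is already completed at pre-test, so no extra women, visits or data are needed.

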The research team will try to finish all the training sessions before the 16th week of pregnancy and conduct the posttest in two phases (the first one immediately after the intervention and the second one during the third trimester of pregnancy [6 months after the intervention]). The participants will be asked to complete the questionnaires once again in the posttest and explain the delivery method and the reason for choosing it after childbirth. Until the end of the study, we will be in touch with the participants to the retention and follow‐up completely in the WhatsApp group.

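### A normality test on the data decides whether the post-intervention ANCOVA is replaced by unnamed nonparametric tests, and the repeated-measures ANOVA is run within each arm, so the time course is not compared between arms

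*Protocol article*

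**What the plan says.** Section 3.8.9 opens with a gate: "After checking the normal distribution of data by the Kolmogorov–Smirnov test, the data will be statistically analysed in SPSS". Near its end comes the consequence: "It is noteworthy that nonparametric tests will be used if the data are not normally distributed". The nonparametric tests are not named, and nothing says whether adjustment for the baseline score survives the switch.

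Between arms, the "mean scores of SOC and FOC will be compared by the independent sample" t "test and ANCOVA, respectively". The natural reading is a t test on pre-intervention scores and ANCOVA on post-intervention scores, with the baseline score as covariate, although the covariate is not written out.

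Repeated-measures ANOVA with the Greenhouse–Geisser correction is then added, to compare pre- and post-intervention "mean scores of SOC and FOC in each of the two groups". No arm-by-time term is mentioned.

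Section 3.8.4 sets two post-tests: "the first one immediately after the intervention and the second one during the third trimester of pregnancy". With baseline, that makes three time points. Section 3.8.9 does not say which post-test the ANCOVA uses.

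Fear of childbirth is a primary outcome and sense of coherence the secondary outcome (3.8.7). The objectives (3.3) compare the intervention and control groups. Sections 2 and 3.5.1 both say that fear peaks in the third trimester.

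**The concern.** Two stated rules are involved.

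**The gate.** ANCOVA relies on roughly normal residuals, not on normal raw scores, and at about 30 per arm it tolerates moderate skew. Here a p-value from the trial's own data can change the analysis of a primary outcome from an adjusted mean difference to something unspecified. If that turns out to be an ordinary two-group rank test on post-intervention scores, the baseline measurement is thrown away.

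**The within-arm ANOVA.** It is the only analysis described that spans the time points, and it looks at each arm separately. By the document's own account fear is at its height when the second post-test is taken, so control women may change too. A change in one arm cannot separate that natural course from an effect of the training. The risk is a report that fear changed significantly with training and not in controls, read as evidence of efficacy.

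**Working it through.** **Plan's own figures (3.8.8).** Means 23 and 20, SDs 4.8 and 3.7, two-sided 5%, power 80%:

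n = (1.96 + 0.8416)² × (4.8² + 3.7²) / (23 − 20)² = 7.849 × 36.73 / 9 = 32.03 per arm; 32.03 × 1.2 = 38.4, which matches the stated 38.

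Pooled SD = √(36.73/2) = 4.285, so the planning effect is 3/4.285 = 0.70 SD. With 20% attrition, 38 × 0.8 = 30.4, so 30 completers per arm are used below. Unadjusted power at 30 per arm is 77%.

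**Assumptions not in the document.** Baseline-to-post correlation r = 0.3, 0.5, 0.7; normal scores, or moderately skewed ones (gamma, shape 4). The fallback is taken to be Mann–Whitney on post scores. The gate is a Kolmogorov–Smirnov test with Lilliefors correction at 5% on post scores in each arm, switching if either rejects. Each row is 4,000 simulated trials (Monte Carlo standard error below 1 point).

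**Power at 0.70 SD, 30 per arm (%):**

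| Scores | r | ANCOVA always | Mann–Whitney always | Rank ANCOVA always | Two-stage rule | Switch fires |
|---|---|---|---|---|---|---|
| Normal | 0.3 | 79.8 | 73.2 | 77.4 | 79.0 | 10.3 |
| Normal | 0.5 | 85.9 | 72.6 | 83.2 | 84.4 | 10.4 |
| Normal | 0.7 | 96.2 | 73.5 | 94.2 | 94.0 | 9.8 |
| Skewed | 0.3 | 78.9 | 79.6 | 83.3 | 80.6 | 44.2 |
| Skewed | 0.5 | 86.0 | 80.5 | 89.0 | 84.5 | 44.9 |
| Skewed | 0.7 | 95.4 | 79.8 | 96.6 | 88.7 | 45.7 |

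The switch rate with normal data is as expected: 1 − 0.95² = 9.75%.

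*Unadjusted rank test against ANCOVA:* a loss of 6.6, 13.3 and 22.7 points with normal scores. With skewed scores, a gain of 0.7, then losses of 5.5 and 15.6 points.

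*Whole two-stage rule against ANCOVA always:* −0.8, −1.5, −2.2 (normal); +1.7, −1.5, −6.7 (skewed). At 0.50 SD the worst case is skewed scores with r = 0.7: 65.6% against 74.7%, a loss of 9.1 points.

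*Type I error of the two-stage rule:* 5.0–5.5% in all six settings.

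**Within-arm tests.** Suppose both arms change equally and the arms do not differ. If each arm's test has power p, the chance that exactly one is significant is 2p(1 − p), which cannot exceed 50%. A paired t test (the two-time-point version of the planned ANOVA) with 30 per arm and equal changes of 0.2 to 0.5 SD gives 13% to 50% over r = 0.3 to 0.7. The low end is a change of 0.5 SD at r = 0.7, where p is about 0.93: 2 × 0.93 × 0.07 = 0.13. The high end is illustrated by a change of 0.35 SD of the change score: p = 0.458, and 2 × 0.458 × 0.542 = 0.496. In about half of these trials the significant arm is the intervention arm.

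**The case against.** **The power loss is conditional.** The plan keeps ANCOVA unless the gate rejects. A reader might infer that 7 to 23 points of power are simply lost. That holds only if the switch fires (about 10% of trials with normal scores, about 45% with the assumed skew) and leads to an unadjusted test. This objection stands.

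**The baseline need not be discarded.** No nonparametric test is named. A baseline-adjusted rank ANCOVA fits the sentence equally well and keeps most or all of the power (table above). A condensed article may leave that name to the analysis plan. This also stands. What remains is that the written rule replaces the ANCOVA on the strength of a preliminary test, with nothing to hold the adjustment in place.

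**The correlation may be low.** Baseline is at 6–12 weeks of gestation and the second post-test is in the third trimester. At r = 0.3 with skewed scores even a forced switch costs nothing. This is fair, and the range above includes it.

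**No error-rate harm.** A reader might infer that choosing the test from the data inflates false positives. The simulated type I error of 5.0–5.5% does not support that.

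**The arms are compared.** A reader might infer that there is no between-arm analysis of scores. There is: the ANCOVA, with the within-arm ANOVA presented as an addition. The article nowhere says that efficacy will be judged from significance in one arm alone, and nothing bars an ANCOVA at each post-test. Only the time course lacks a stated between-arm comparison.

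**Delivery method.** The section says: "The two groups will also be compared before and after the intervention using a" chi-square test. A reader might call it an error to ignore the pre-test choice. Under randomisation the unadjusted comparison after the intervention is valid; adjustment is an optional gain in precision.

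**Conclusion.** The point holds in a limited form. A preliminary normality test on the data can displace the ANCOVA of a primary outcome in favour of tests that are not named, and the repeated-measures analysis is described within arms with no arm-by-time comparison, although the trial's questions are between-arm.

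The expected cost of the gate is small to moderate: from about +2 to about −9 power points over effects of 0.50 to 0.70 SD and r of 0.3 to 0.7. The larger gap, about 73% against 80–96% with normal scores, applies only if the switch leads to an unadjusted rank test. These figures rest on the assumed correlations, skew and fallback test. The 0.70 SD is itself borrowed from the meaningfulness figures used in the sample size section, not from the fear scale.

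The 13–50% range for the within-arm tests shows why they cannot stand in for an arm comparison. It is not a false-positive rate of the trial's between-arm analysis. The weakness is worth correcting before analysis, but it does not invalidate the trial.

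**What to change.** 1. Keep baseline-adjusted ANCOVA as the between-arm analysis of both scales whatever the normality test shows, and name the baseline score as covariate. Check residuals instead of raw scores. As a sensitivity analysis, use robust or bootstrap standard errors for the same model, or a baseline-adjusted rank ANCOVA.

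2. Replace the within-arm repeated-measures ANOVAs with one model per scale over both post-tests, containing arm, time, arm-by-time and baseline score. Report the arm difference with its 95% confidence interval at each post-test.

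3. Optionally, adjust the delivery-method comparison for the choice recorded at pre-test. The planned chi-square test is valid without this.

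The cost is a change of wording and a little more analysis work, with no new data and no change in sample size. The one downside is a model-based estimate in place of a rank test when scores are skewed, which the sensitivity analysis covers.
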